## Statistical analysis

All primary statistical analysis will use the intention-to-treat principle. The primary endpoint will be analysed using a mixed model with time, treatment, time × treatment interaction as fixed effects, baseline measurement as covariate, and patient as random effect. The treatment difference at 12 months together with its 95% confidence interval will be derived from the mixed model.

Missing data will be treated as missing at random in the above mixed model analysis and no imputation will be made. To assess the sensitivity of the result to this assumption, the last observation carried forward (LOCF) strategy will be used to compute the missing HAI at during the follow up visits. Other assessments will be analysed in a similar way.

The primary economic evaluation will only include those for whom complete data at baseline, 12 and 24 months follow-up are available. Sensitivity analysis will then include those cases with missing data, where LOCF will be used to account for missing data. The following baseline characteristics of study participants with available and unavailable service use data will be compared: centre, gender, living arrangements, ethnicity, marital status, education, EQ-5D.

For each piece of service use information collected with the AD-SUS, a unit cost will be applied and the total costs calculated. The total cost per participant is calculated by summing all costs. All unit costs will be for the financial year 2008-2009. Costs in the second year will be discounted at a rate of 3.5%, as recommended by the National Institute for Health and Clinical Excellence [28].

The difference in mean costs between active treatment and control groups together with the 95% confidence interval will be derived. The equivalence margin is pre-specified as £150. The equivalence will be declared between active and control groups in terms of secondary economic outcome if the 95% confidence interval falls within (-£150, +£150).

Even in situations where equivalence or non-inferiority are demonstrated, exploration of the joint distribution of costs and effects in a cost-effectiveness analysis (CEA) is recommended to represent uncertainty [29] and to help interpret the economic results. For these reasons, we propose to undertake a CEA irrespective of whether or not non-inferiority in the primary clinical outcome is demonstrated. Cost-effectiveness will be assessed using the net benefit approach [30] with reference to Bosmans' methods (31) for economic evaluations alongside equivalence or non-inferiority trials.

The cost-effectiveness analysis will use the primary outcome measure the HAI and a cost-utility analysis will be completed using QALYs derived from the EQ-5D data. A number of one-way sensitivity analyses will test the robustness of the results to the assumptions made in the economic evaluation.

The numbers (with percentages) of losses to follow-up at 12, and 24 months after randomisation will be reported and compared between the treatment arms with absolute risk differences (95% Confidence Intervals). Deaths will be reported separately for each group. The CONSORT procedure will be used for reporting flow through the trial.

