## Sample size

We calculated sample sizes for both the primary outcome measure and the first secondary outcome measure, choosing the larger of the two for the study.

Based on the pilot study in a genitourinary medicine clinic [10], we assume that the true difference in the change of HAI between CBT and control at 1 year is 5.00 points and that the standard deviation for the change of HAI at 1 year is 7.58 points. With the above assumptions, the study will need 122 patients to detect the above difference with 95% power at a two sided 5% significance level. Taking into account an estimated drop-out rate of 20% drop-out, the sample size is therefore estimated to be 152 patients.

There remains no agreed approach to calculate the sample size required for an economic evaluation, particularly in areas such as health anxiety in which the willingness to pay for improvements in outcomes is unknown. Based on the pilot study, we considered that the CBT intervention would be cost-effective if it improved HAI score and was no more costly than the control treatment. The sample size calculation for the economic evaluation was therefore based on the total costs over 24 months being equivalent.

With a sample size of 186 per group, the study will have 80% power to reject the null hypothesis that the cost of the CBT and control are not equivalent (where the difference in mean costs is +/- £150) in favour of the alternative hypothesis that the means of the two groups are equivalent, assuming the expected difference in means is £0 and the common standard deviation is £580 (from pilot data).

The sample size is thus powered by the first secondary outcome of the CHAMP study, estimated as 466 patients, assuming a 20% drop-out by 24 months, leading to an estimated total of 372 completed with equal randomisation between groups. Thus with 466 patients, or fewer if the drop-out rate is less, the study is adequately powered to both detect the assumed difference in the primary outcome and assess the equivalence in the secondary economic outcome between CBT and control group. The analysis will close on the date on which the last patient has completed the two year follow-up.

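### LOCF, the named check on the missing-at-random assumption for HAI, tests one fixed alternative and not graded departures, so it is weak evidence of robustness

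*Protocol article*

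**What the plan says.** The Statistical analysis section of the protocol article sets out the primary HAI model: "The primary endpoint will be analysed using a mixed model with time, treatment, time × treatment interaction as fixed effects, baseline measurement as covariate", with patient as a random effect. The treatment difference is read off at 12 months. On missing values it says: "Missing data will be treated as missing at random in the above mixed model analysis and no imputation will be made". The check on that assumption follows directly: "To assess the sensitivity of the result to this assumption, the last observation carried forward (LOCF) strategy will be used", applied to missing HAI scores at the follow-up visits. The approach is then extended: "Other assessments will be analysed in a similar way".

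The article names no other analysis of how the HAI result depends on MAR. It does promise losses to follow-up by arm at 12 and 24 months with risk differences, but that describes attrition and does not examine the treatment effect. The comparison of participants with and without data concerns service use, not HAI. The economic evaluation has its own LOCF step ("Sensitivity analysis will then include those cases with missing data, where LOCF will be used to account for missing data"), which is a separate matter and is not pursued here.

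**The concern.** A sensitivity analysis for MAR should let the unobserved outcomes be worse or better than MAR predicts by a stated amount, and show when the conclusion gives way. LOCF does not do this. It holds each patient who leaves at the last recorded score (baseline, 3 or 6 months for the 12-month endpoint) and then treats the filled-in value as observed. The result depends on the shape of the trajectories and on the timing and arm of drop-out, and these have no fixed relation to a failure of MAR.

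The plausible threat here is that patients leave CBT because they are not improving, or do badly after leaving. The useful question is how much worse they would have to be. If LOCF agrees with the mixed model, readers may be reassured without good reason. If it disagrees, the cause may be LOCF's own bias and not a failure of MAR.

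**Working it through.** Benefit is given as points of HAI in favour of CBT.

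**Inputs from the Sample size section.** "the true difference in the change of HAI between CBT and control at 1 year is 5.00 points"; "the standard deviation for the change of HAI at 1 year is 7.58 points"; 20% drop-out; 372 completers, so 186 per arm. The Current status section gives 444 randomised and early drop-out below 10%.

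**The plan's own figure.** It states "the study will need 122 patients to detect the above difference with 95% power at a two sided 5% significance level". The normal approximation gives n per arm = 2 × [7.58 × (1.960 + 1.645) / 5]² = 59.7, so 60 per arm or 120 in total, within two patients of 122. Power at 61 per arm is 95.4%. Inflation gives 122 / 0.8 = 152.5, stated as 152. The planning inputs are therefore usable, and the HAI sample size is not in question.

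**How LOCF moves the estimate.** If a fraction f leaves after month 3 in both arms, unrelated to score, LOCF reports (1 − f) × (12-month effect) + f × (3-month effect). Take f = 0.2 and a 12-month effect of 5. The 3-month effect is not in the document, so a range is shown:
- 3-month effect 1: 0.8 × 5 + 0.2 × 1 = 4.2
- 3-month effect 5: 5.0
- 3-month effect 8 (early gain, later relapse): 0.8 × 5 + 0.2 × 8 = 5.6

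**Simulation.** 233 per arm, 1,000 trials per scenario, HAI at 0, 3, 6, 12 and 24 months, SD of 12-month change 7.58, drop-out depending on the last observed HAI. The mean trajectories, the correlations (0.6 between visits, 0.4 with baseline), the baseline SD (4.5) and the split of drop-out by arm are assumptions.

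When MAR holds and the true effect is about 5, the mixed model gave 4.96 to 5.03 throughout. LOCF gave:

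| Trajectory | Nominal drop-out | LOCF |
|---|---|---|
| Gradual gain | 10% each arm | 4.80 |
| Gradual gain | 20% each arm | 4.55 |
| Gradual gain | CBT 30%, control 10% | 3.62 |
| Gradual gain | CBT 10%, control 30% | 5.46 |
| Early gain, relapse | 20% each arm | 5.24 |
| Early gain, relapse | CBT 10%, control 30% | 6.12 |

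With no true effect and the same improvement in both arms, LOCF was unbiased to within 0.03 points when the nominal drop-out was equal. It showed a spurious benefit of 0.62 with control 25% and CBT 15%, and of 1.24 with control 30% and CBT 10%.

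When MAR fails (gradual gain, about 19% missing at 12 months):

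| CBT drop-outs worse than MAR predicts by | True effect | LOCF |
|---|---|---|
| 0 | 5.03 | 4.55 |
| 3 points | 4.51 | 4.57 |
| 8 points | 3.59 | 4.53 |

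LOCF stays put because it uses only observed scores. The MAR model stays put for the same reason (5.03 and 4.99 in the last two rows). That is why the assumption about the unseen scores has to be varied deliberately.

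**Standard error at 20% drop-out, gradual gain.** The LOCF mixed model reports 0.70. The MAR model reports 0.76, the analysis with no missing data 0.69, and the actual sampling SD of the LOCF estimate is 0.73. So 0.70 / 0.76 = 0.92 (8% below) and 0.70 / 0.73 = 0.96 (4% below).

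**Tipping point, CBT arm shifted alone.** The effect falls by about f × delta, with the standard error held fixed.
- SE = 7.58 × √(2/186) = 0.786, and 1.96 × 0.786 = 1.54.
- Difference 5, f = 0.2: (5 − 1.54) / 0.2 = 17.3 points.
- Difference 2.5, f = 0.2: (2.5 − 1.54) / 0.2 = 4.8 points.
- If drop-out were 10% at 12 months (assumed), about 200 of 222 per arm are observed. SE = 7.58 × √(2/200) = 0.758 and 1.96 × 0.758 = 1.49. The tipping points become (5 − 1.49) / 0.1 = about 35 and (2.5 − 1.49) / 0.1 = about 10.

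**The case against.** The strongest defence is that LOCF is only the secondary analysis. The primary estimate comes from the MAR mixed model, which recovered the truth in every MAR scenario. This stands.

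LOCF also has some content. It holds a non-improving CBT patient at an unimproved score, which is roughly the feared scenario, and in the 3-point case it landed near the truth (4.57 against 4.51). A reader might infer that the LOCF comparison says nothing at all about MAR. That goes too far: it tests one alternative. But the closeness depends on the assumed trajectories, and the 8-point case was missed by almost a point.

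A reader might also infer that LOCF is bound to be biased, with seriously understated standard errors. The document does not support that. Bias disappeared with no effect, common trajectories and equal nominal drop-out. The largest biases needed 30% against 10% drop-out, an imbalance the document does not suggest. The standard-error shortfall is modest, and in a single-visit ANCOVA on LOCF data at 20% drop-out it was negligible (0.72 against a sampling SD of 0.73).

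The Background section says untreated symptoms tend to persist, which favours carrying scores forward. That applies to untreated patients, whereas the trial's hypothesis is change under CBT, and the Discussion lists maintenance of benefit among the questions for follow-up.

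Finally, telephone interviews and early assessments (Assessments section) should limit missing data, and an analysis plan not shown may add analyses. Both are fair. Even so, LOCF is the check this document names.

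**Conclusion.** The point holds as a weakness in the chosen sensitivity analysis. LOCF examines a single no-change assumption, can err in either direction when MAR is true, and somewhat understates uncertainty. It therefore gives weak evidence about robustness to MAR for HAI and, by extension, for the other assessments.

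A reader might infer that the primary conclusion is in danger. The document's own figures point the other way. At planning values the tipping point of about 17 points exceeds two SDs of change (2 × 7.58 = 15.2), and it rises with less drop-out. The exposure lies elsewhere: a smaller observed effect (about 5 points at a difference of 2.5 with 20% missing), unequal drop-out, the 24-month results and the secondary scales.

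The tipping points rest on a fixed standard error and a shift in the CBT arm alone. The LOCF bias and standard-error figures rest on assumed trajectories, correlations and drop-out patterns. Their sizes are illustrative, but the mechanism is general.

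**What to change.** Make the MAR sensitivity analysis for HAI at 12 months a delta-adjusted multiple imputation:

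- Impute under MAR separately by arm.
- Worsen the imputed values by delta, first in the CBT arm alone, then in both arms. The second version moves the estimate only by delta times the difference in missing fractions, so it is informative mainly when drop-out is unequal.
- Increase delta in steps until the conclusion changes or the limit of the scale is reached. A fixed ceiling such as 10 points would stop short of the 17-point tipping point at planning values.
- Report the tipping point.

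A control-based (reference) estimate may be added. LOCF may stay as a supplementary result, but should no longer be described as the check on MAR. Apply the same approach to the other continuous scales.

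The cost is revised plan wording and a little extra analysis work. The primary model, sample size, visits and data collection do not change.

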The remaining clinical assessments, in addition to the main health anxiety one (HAI) examined the presence of generalised anxiety and depression (measured with the HADS scale [14]) as these are common in patients with hypochondriasis, and also adversely affects quality of life (EQ-5D)[15], and social functioning (SFQ)[16]. These assessments were given at baseline and at 6m, 12m and 24m (or earlier and at intervening periods if drop-out or loss to follow-up was likely). To ensure the highest possible follow-up the intention was to contact patients after 18 months to be reminded of the 2 year assessment, and if for any reason (eg being out of the country), the final assessment might be made earlier. The HAI was also given at 3 months by post or by telephone with a research assistant. Service use data for the economic evaluation was collected using the Adult Service Use Schedule (AD-SUS), an interviewer-assessed instrument designed by one of the applicants and based on previous economic evaluations in adult mental health populations [22,23], and also by examination of computerised hospital records. AD-SUS data were recorded at baseline and at 6, 12 and 24 months. Where the AD-SUS data conflict with the data obtained from the computerised records the AD-SUS data will take precedence only when it refers to a contact at a hospital not included in the electronic data search, as the details of admission and investigations is more likely to be correct from official records than from personal retrospective recall. Data on workplace absenteeism and presenteeism [24] were also recorded at 6, 12 and 24 months follow-up. In addition the SCID-I hypochondriasis questions [17] are to be administered again at 24 months to determine if each patient still satisfies the requirements for DSM-IV hypochondriasis. All these instruments are given at face to face interview but also have the advantage that they can be given over the telephone if necessary, and this can be useful in reducing loss to follow up. All assessments are carried out by independent research assistants who have had no contact with the patient at other times and who are carefully masked to avoid disclosure of allocation (see below).

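### The main cost comparison leaves out randomised patients with incomplete data, and its only stated remedy, last observation carried forward, does not suit a summed 24-month cost

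*Protocol article*

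**What the plan says.** The Statistical analysis section opens with a general rule: "All primary statistical analysis will use the intention-to-treat principle". For the Health Anxiety Inventory it then specifies a mixed model that uses the available follow-up under a missing-at-random (MAR) assumption, without imputation. Other assessments are to be handled similarly.

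Costs follow a different rule. The section states "The primary economic evaluation will only include those for whom complete data at baseline, 12 and 24 months follow-up are available", and then "Sensitivity analysis will then include those cases with missing data, where LOCF will be used to account for missing data". It gives no other method for missing cost data. On the endpoint it says "The total cost per participant is calculated by summing all costs". Equivalence is declared if the 95% confidence interval for the difference in mean cost lies within ±£150.

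The Sample size section explains that the economic calculation was "based on the total costs over 24 months being equivalent", and this calculation fixed the size of the trial. Research objectives lists two-year cost as hypothesis (ii) of the two main hypotheses. The abstract and Sample size call the same outcome secondary.

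On data sources, the Assessments section says "AD-SUS data were recorded at baseline and at 6, 12 and 24 months". Service use is collected by this interview "and also by examination of computerised hospital records". The records take precedence except for contacts at hospitals outside the electronic search. For patients who may be unavailable at two years, "the final assessment might be made earlier".

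**The concern.** A cost comparison limited to patients with full data is unbiased only if those patients represent everyone randomised, or if whatever makes them differ is unrelated to cost and arm. The plan gives no reason to expect that. It does not make the same demand of the clinical endpoint, where partly observed patients contribute.

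The remedy is the second difficulty. LOCF was devised for a score measured at a point in time. A 24-month cost is a sum over periods, and here the periods differ in length. A sensitivity analysis with its own distortion cannot show whether the complete-case result is safe.

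The stake is an equivalence claim judged against a margin of £150. A modest shift in the difference, or a narrower interval because costly patients happen to be missing, could change the conclusion. Whether costly patients are in fact the ones missing is unknown.

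**Working it through.** **1. Who is left out.** Inputs from Sample size: 186 per group, 372 completers, 20% loss, 466 randomised. Check of the plan's figure: 372 / 0.80 = 465, against 466 stated (466 × 0.80 = 372.8). The plan's total is reproduced to within rounding.

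- Planned: 466 × 0.20 = 93.2, so about 93 patients outside the primary cost comparison.
- With the 444 randomised (Current status of trial): 444 × 0.20 = 88.8, about 89.
- If loss stayed at 10%: 444 × 0.10 = 44.4, about 44.

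**2. Precision.** Losing 20% raises the standard error by 1/√0.80 = 1.118, or 12%. The inflation from 372 to 466 was made for exactly this, so it is not an additional cost of the complete-case rule. What remains is bias.

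**3. LOCF on a summed cost.** Interviews at 6, 12 and 24 months define periods of 6, 6 and 12 months. Take a constant monthly cost r.

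- True total: 6r + 6r + 12r = 24r.
- Month 24 missing, month 6-12 amount carried forward unchanged: 6r + 6r + 6r = 18r.
- Ratio 18/24 = 0.75, a shortfall of 25% for that patient.
- With second-year costs discounted at 3.5%, as the plan specifies: (12 + 6/1.035) / (12 + 12/1.035) = 17.80 / 23.59 = 0.754. Discounting changes little.
- If a rate is carried instead (month 6-12 cost × 2): 6r + 6r + 12r = 24r, and the length error disappears.

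**4. What that does to the comparison.** The documents give no mean 24-month cost, so assume a range of £1,000 to £4,000.

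- Arm mean, 20% of the arm missing only the last period: 0.25 × 0.20 × mean = £50 to £200 too low.
- Difference, equal missingness and equal costs in both arms: the shortfalls cancel.
- Difference, missingness 10 percentage points apart: 0.25 × 0.10 × mean = £25 to £100, against a £150 margin.

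The cost range and the missingness patterns are illustrations, not figures from the plan.

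**5. Timing of savings.** Background reports that, in the pilot, lower costs appeared only in the six months after treatment ended. Discussion justifies the two-year follow-up by longer-term savings. Any form of LOCF, including a carried rate, fills the later period with the earlier one. It therefore assumes away the change over time that the trial was extended to observe.

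**6. The completeness rule.** Interviews take place at 6, 12 and 24 months, but completeness is defined by baseline, 12 and 24. Costs for months 0-6 enter the sum. Unless the 12-month interview also covers that period, a patient with no 6-month interview would count as complete while missing a quarter (6/24) of the follow-up time. Recall windows are not stated, so this is a gap in the rule and not a demonstrated error.

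**The case against.** Several defences carry weight.

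- **Intention to treat.** The opening rule covers primary analyses, and cost is labelled secondary in several places. Nothing suggests that patients would be analysed other than as allocated. A reader might infer a flat contradiction, but the text does not go that far. Still, the outcome is a main hypothesis, it sized the trial, and the analysis is itself called primary, so the exclusion sits badly with the principle.
- **Scale.** Early drop-out is reported as below 10%, so 93 may be too high. That figure describes early follow-up only, but the lower count of about 44 must be shown beside it.
- **LOCF wording.** The article does not say whether an amount or a rate is carried. The 25% applies to one reading and one type of patient, and need not reach the between-arm difference.
- **Checks already planned.** The article compares baseline characteristics of those with and without service-use data, compares losses between arms, and plans one-way sensitivity analyses. These describe possible selection; they do not correct it.

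Stronger inferences are tempting and should not be drawn. The article does not say that patients who die are dropped from the cost set. It does not say that an early final interview counts as full 24-month cost data, or that the record search stops there. It does not say who is most likely to be missing. A reader might also argue that, for a patient last seen at 6 months, therapy cost would be counted three times. That holds only if therapy cost lies within the carried amount, and the costing rule is not given.

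**Conclusion.** The point holds as a concern about bias in the comparison that sized the trial. The main cost analysis sets aside randomised patients whom the clinical analysis would use as far as they were observed: about 93 of 466 at the planned loss, about 44 of 444 at 10%. The stated fallback is unsuitable for a cumulative cost. Carried forward unchanged, it is 25% low for a patient missing only the last period, assuming constant accrual. Carried as a rate, it still replaces later costs with earlier ones. The effect on the equivalence result cannot be fixed from the article. It is near zero from the length error if costs and missingness match across arms, and £25 to £100 under the assumed costs with a 10-point imbalance. The direction of the complete-case bias is unknown.

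**What to change.** Before the two-year cost data are compared by arm, amend the plan as follows.

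- Define the primary cost comparison as all randomised patients, as allocated.
- Take hospital costs from the planned computerised records to 24 months, or to death, where available, whether or not the interview was held.
- Multiply impute missing AD-SUS period costs separately by arm, using baseline cost, centre, EQ-5D and the observed period costs. Treat any stretch of follow-up that no interview or record covers as missing.
- State the period that each interview covers, and name the 6-month data in the definition of completeness unless the 12-month interview covers it.
- Keep the complete-case analysis as a sensitivity analysis and remove LOCF for costs.

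The cost is a change of wording and modest extra analysis of data already being collected. Two limits remain: imputation rests on a MAR assumption, and the records will be incomplete for hospitals outside the electronic search.

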### Inclusion and exclusion criteria

Patients suitable for inclusion were those who satisfied the criteria for excessive health anxiety above and were (i) aged between 16 and 75, (ii) permanently resident in the area, (iii) had sufficient understanding of English to read and complete the questionnaires, and (iv) had given written consent for the interviews, audio-taping of 50% of treatment sessions, and for access to their medical records. The presence of existing medical pathology, provided it was not new and requiring further investigation, was not a bar to treatment in the study. This decision was made as in an earlier study we found that many patients with existing pathology who also had high health anxiety benefited from the intervention [10].

Some of those who would otherwise satisfy the inclusion criteria above were excluded if (i) they were felt by their consultants to have a level of continuing major pathology that was too severe for them to take part in the study, (ii) they were currently being actively investigated for significant pathology suspected by the clinician and for whom cognitive behaviour therapy might confuse or cause distress, (iii) they had significant cognitive impairment, and (iv) they were currently under psychiatric care.

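### The primary economic evaluation is confined to patients with complete data, despite an intention-to-treat statement for all primary analysis, and the LOCF sensitivity analysis does not make up for it

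*Protocol article*

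**What the plan says.** In the protocol article, the Statistical analysis section opens with a general commitment: "All primary statistical analysis will use the intention-to-treat principle". For the HAI, the mixed model keeps patients with partial follow-up: "Missing data will be treated as missing at random in the above mixed model analysis and no imputation will be made". For costs the rule is different: "The primary economic evaluation will only include those for whom complete data at baseline, 12 and 24 months follow-up are available". The next sentence covers the rest: "Sensitivity analysis will then include those cases with missing data, where LOCF will be used to account for missing data". The section also plans to compare baseline characteristics of patients with and without service-use data, and losses to follow-up between arms.

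The Assessments section names two sources of service use. One is the AD-SUS interview: "AD-SUS data were recorded at baseline and at 6, 12 and 24 months". The other is introduced with the words "and also by examination of computerised hospital records". Where the two conflict, the records prevail for hospitals in the electronic search, "as the details of admission and investigations is more likely to be correct from official records than from personal retrospective recall". Inclusion and exclusion criteria makes written consent a condition of entry for interviews, audio-taping "and for access to their medical records".

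The Sample size section bases the trial's size on total cost over 24 months: 186 per group, and 466 randomised after a 20% allowance for drop-out.

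**The concern.** The outcome that sized the trial has the most restrictive analysis set in the plan. An intention-to-treat comparison concerns everyone randomised, whereas the economic comparison as written concerns those who supplied complete data. If the patients who drop out of the CBT arm differ in cost from those who stay, and the same is not true of the control arm, the difference tested against ±£150 is no longer the one that randomisation protects. The cost-effectiveness and cost-utility analyses would have the same weakness.

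The rule also sets aside information. A patient seen at 6 and 12 months but not at 24 has interview-based costs for the first year and is still excluded. Hospital records do not depend on attending an interview, so part of a non-attender's cost may be obtainable for the missed period as well.

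**Working it through.** **Inputs (protocol article).** Sample size: SD £580, true difference £0, margin ±£150, 186 per group, 80% power, 20% drop-out, 372 completing, 466 randomised. Current status of trial: 444 randomised, early drop-out below 10%.

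**1. Reproducing the plan's figure.** With a single one-sided 5% test, n per group = 2 × 580² × (1.645 + 0.842)² / 150² ≈ 185. The t-based version gives 80.1% power at 186. Then 372 / 0.80 = 465, or 466 for equal arms. The stated figures reproduce. Because 372 is the number expected to complete, the stated power already refers to a complete-case set.

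**2. Patients excluded.**
- 466 − 372 = 94.
- 444 × 0.20 ≈ 89.
- 444 × 0.10 ≈ 44.

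**3. Precision.** SE = 580 × √(2/n); power = Φ(150/SE − 1.645), the formula that reproduces 186.

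| Scenario | n per group | SE | Power |
|---|---|---|---|
| 466 randomised, 20% excluded | 186 | £60.1 | 80.2% |
| 466 randomised, all included | 233 | £53.7 | at most 87.4% |
| 444 randomised, 20% excluded | about 178 | £61.5 | 78.6% |
| 444 randomised, 10% excluded | about 200 | £58.0 | 82.7% |
| 444 randomised, all included | 222 | £55.1 | at most 86.0% |

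The all-included rows are upper bounds. They treat every added patient as fully observed, whereas records give only part of total cost.

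**4. Bias.** If a fraction p is excluded in each arm, then

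complete-case difference − all-randomised difference = p × (difference among completers − difference among those excluded).

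The documents give no value for the bracket. As an assumption, take £375:
- p = 0.20 gives £75, half the margin.
- p = 0.10 gives £37.50, a quarter of the margin.

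If the bracket is zero there is no bias. This shows sensitivity to the assumption and does not estimate the bias.

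**5. Does LOCF repair it?** LOCF fills a missed period with an earlier period's cost and ignores any hospital record for the missed period. The Background section reports that, in the secondary-care pilot, cost reductions appeared only in the six months after treatment ended, so an earlier cost is a poor stand-in for a later one. The visits are also unevenly spaced. If each interview covers the time since the last (an assumption), a 6-to-12-month cost carried into the 12-to-24-month period stands for half that period's length unless it is rescaled.

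**The case against.** The strongest reply is that a complete-case primary analysis with an all-patient sensitivity analysis is openly pre-specified, that the plan compares patients with and without service-use data, and that cost is a secondary outcome. The plan also works to limit loss, with an 18-month reminder, telephone assessment and the option of an early final assessment. All of this stands and lowers the weight of the point. It does not remove it: describing selection does not correct it, and the one analysis that includes everyone uses a method ill-suited to costs.

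Some stronger readings are tempting but unsupported.

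- **That the rule leaves the trial short of its stated power.** It does not; 186 per group is the number left after 20% loss.
- **That it reduces a low chance of declaring equivalence still further.** Under the 95% confidence interval rule, the chance at zero difference is about 41% with 186 per group and at most 59% with 233. Those figures are correct, but the low starting value arises because 186 reproduces only with a one-sided 5% test. That is a separate matter.
- **That the trial already holds full hospital costs for patients who miss interviews.** The article does not say so. It refers to complete data, not complete interviews. Extraction for non-attenders is an inference from universal consent and a records search that need not depend on attendance. The records cover only the searched hospitals, so total cost stays partly unobserved.
- **That many patients would be lost for an incomplete baseline.** The Abstract, Form of randomisation, and Target population and procedure all place baseline assessment before randomisation, so such losses should be negligible.

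**Conclusion.** The point holds in moderate form. The intention-to-treat statement and the complete-data rule need to be reconciled, and the rule is a weak choice for the primary economic analysis. It excludes up to about 20% of randomised patients (94 of 466, or 89 of 444), or about 44 of 444 if loss is 10%; the below-10% figure in the article describes early follow-up, not 24 months. The main risk is selection bias, whose size cannot be known from the documents and which arises only if the link between loss and cost differs by arm. The precision forgone is modest: about 80% against at most 87% power with 466 randomised, assuming the plan's SD of £580 and a true difference of £0. The HAI analysis is unaffected.

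**What to change.** Define the primary economic analysis on all randomised patients, in the arm to which they were allocated. Take hospital costs from the computerised records wherever they can be extracted, whether or not interviews were attended. Multiply impute the missing AD-SUS components and EQ-5D values, separately by arm, with baseline cost, observed hospital cost, HAI and EQ-5D in the imputation model. Keep the complete-case analysis as a sensitivity analysis and drop LOCF for costs.

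The cost is a change of wording, record extraction for the non-attenders (roughly 44 to 94 patients, with consent already given) and an imputation run. No new visits are needed. The price in assumptions is reliance on missing-at-random for the unobserved components, including contacts at hospitals outside the search.
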